Persons who fall into any of the following categories shall not be used as research subjects.

1. Complications of cardiac disease.
2. Cardiac pacemaker users
3. History of epilepsy
4. Visual acuity (correctable) less than 0.7 in both eyes
5. Air conduction hearing greater than 30㏈.
6. There is tactile hypoesthesia (unable to perceive Semmes-Weinstein monofilament no. 2.83)
7. Perceived significant taste and olfactory abnormalities
8. History of any other visual or hearing impairment, language comprehension disorder, mental disorder, or motor dysfunction that would interfere with the performance of the research task.

The reasons for setting (a) and (b) are because they may affect autonomic measurements and (c) because they may affect electroencephalography measurements. The reason for (d) through (g) is to exclude people with functional abnormalities in the sensory organs to be evaluated and intervened in this study.

Suspension Criteria

1. When the research subject wishes to discontinue
2. When it is deemed appropriate to discontinue other activities.

3) Number of research subjects and rationale for setting the number of research subjects

The target number of patients for this study is 58, consisting of 29 in the intervention group and 29 in the control group.

Regarding the rationale for the setting, this study will conduct a two-group comparison (unpaired t-test, one-tailed) of the intervention and control groups for changes in the parasympathetic index (RSA: respiratory sinus arrhythmia) before and after the intervention as the main outcome. Using G*Power 3.1.9.2 and referring to previous studies^11)12)^ that utilized RSA, the effect size was set to 0.7, with an alpha error of 0.05 and a beta error of 0.20, resulting in a total sample size of 52 participants. In addition, considering the possibility of approximately 10% dropout, approximately 58 subjects will be needed for the study. 58 subjects will be randomly divided into 29 in the SRI group and 29 in the control group.

The number of subjects in the previous study^6)13)^, which investigated parasympathetic indices and sensory processing characteristics in children with ASD and normal children, was 50 and 83, respectively, and we believe that the above number of subjects is generally appropriate.

5. Method of the study and the scientific rationale for the study

1) Design

□ Intervention study

Phase of study: Exploratory study

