Method of comparison: Before/after comparison/parallel group comparison

Method of allocation of intervention: Randomization

Blinding of evaluators: Blinding of only the researcher in charge of statistical analysis.

Therefore, this study is a randomized controlled trial.

2) Method

Those who are willing to participate in the study, agree to participate after receiving a thorough oral and written explanation from the investigator, and meet the eligibility criteria will be enrolled as study subjects. Using an allocation chart, the study administrator will randomly assign the subjects to the SRI group or the control group and implement the intervention. Afterwards, only the subject's ID and data will be sent to the co-researcher in charge of statistical analysis, who will conduct the analysis. In this way, blinding the researcher in charge of statistical analysis minimizes bias and ensures appropriate results.

The flow of implementation is shown in Figure 1. The study consists of six phases: (a) preliminary investigation (screening), (b) initial evaluation, (c) evaluation immediately before the intervention, (d) intervention, (e) evaluation immediately after the intervention, and (f) final evaluation. Each phase is described below. All surveys, evaluations, and interventions will be conducted at Human Health Science, Graduate School of Medicine, Kyoto University.

[figure not shown]

Figure 1: Flow of Implementation

1. Preliminary investigation (screening)

The main purposes of this survey are to screen subjects who are not suitable for the study and to evaluate their psychiatric disorders and sensory processing characteristics. The items measured were (1) basic information of the subjects, (2) medical information, (3) JSI-mini (Japanese Sensory Inventory mini), (4) Autism spectrum Quotient (AQ), (5) Schizotypal Personality Questionnaire (SPQ), and (6) the Japanese Adolescent/Adult Sensory Profile (A/ASP) (see "3) Observation Items and Schedule"). If the eligibility criteria are not met, the subjects will be asked to refrain from further participation in the study, and the experiment will be terminated with an honorarium, based on the time spent in the preliminary investigation. After enrollment of study subjects who meet the eligibility criteria, the subjects will be randomly assigned to two groups, the SRI group and the control group, and will be blinded to the assigned researcher (in charge of statistical analysis) until the end of the analysis.

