After the 30-minute intervention, a post-intervention evaluation was conducted. The evaluation items consist of (1) RSA measurement during the Sensory Challenge Protocol (SCP), (2) EEG measurement, and (3) Profile of Mood States 2nd Edition (POMS2), the same as the evaluation immediately before the intervention (see "3) Observation Items and Schedule"). The order of the procedures is RSA measurement, EEG measurement, and POMS2, in that order. The time required is approximately 60 minutes. We will examine how the intervention changes the subjects' autonomic nervous system function, EEG waveform trends, and subjective mood state in the intervention and control groups, respectively.

1. Final Evaluation

The day after the immediate post-intervention evaluation, the final evaluation will be conducted. The final evaluation will be conducted using the CAB (1) conducted in the initial evaluation (see "3) Observation Items and Schedule"). The time required is approximately 30 minutes. We will examine how the intervention changed the cognitive function of the subjects in the intervention group and the control group.

3) Observation, inspection, investigation, and reporting items and schedule

- Measurement item, measurement method, person or organization

The measurement items and methods are described below. All measurements are performed by the researcher.

1. Items to be conducted in the preliminary investigation

The following will be heard and evaluated. The time required is 30 minutes.

1. Basic information of the subjects (age, gender, educational and occupational history, handedness, intellectual function) (Ref. 3): The Japanese version of the FLANDERS Handedness Test (Ref. 4) is used to assess handedness, and the JART (Japanese Adult Reading Test) (Ref. 5) to assess intellectual function.
2. Medical information (history, current medical history, visual acuity, hearing, touch, taste, and smell) (Ref. 3): Visual acuity was assessed using the International Standardized Visual Acuity Test at 5 m, hearing using the Mimi Hearing Test, and touch using the Semmes-Weinstein monofilament.
3. JSI-mini (Japanese Sensory Inventory mini) (Ref. 2): A simplified version of the JSI-R (Japanese Sensory Inventory Revised), with 20 self-administered items. It is a simple way to grasp the tendency to receive sensory stimuli.

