The experimental flow is shown in Figure 2. The evaluation and intervention will be conducted over three days: on the first day, after explanation and consent, a preliminary survey and initial evaluation will be conducted; on the second day, the evaluation immediately before the intervention, the intervention, and the evaluation immediately after the intervention will be conducted; and on the third day, the final evaluation will be conducted. Each evaluation item will be conducted with appropriate breaks in between.

[figure not shown]

Figure 2: Measurement schedule

4) Summary of analysis

- - Primary Endpoint

(a) Differences in the variability of RSA values due to sensory stimulation of SCP before and after the intervention.

- - Secondary endpoint

(a) EEG amplitude differences before and after intervention, (b) POMS2 score differences before and after intervention, (c) CAB score differences at initial and final assessment, (d) correlation between AQ scores and RSA values, (e) correlation between SPQ scores and RSA values, (f) correlation between A/ASP scores and RSA values, (g) power spectrum by EEG band during intervention, (h) RSA power spectrum of each EEG band, (h) RSA during intervention

- - Main Analysis Methods

The statistical significance level is set at p < 0.05. A one-tailed test is used.

Basic information, medical information, and observation records during the use of the sensory room were compiled as descriptive statistics: RSA values were calculated as the difference between the SCP resting period and the mean value during each sensory stimulus; EEG amplitudes were obtained by subtracting the standard stimulus waveform from the deviant stimulus waveform of the presented task to obtain the amplitude of the positive or negative component during latencies of approximately 200 to 400 ms. The EEG amplitude is obtained by subtracting the standard stimulus waveform from the deviant stimulus waveform of the presented task.

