The experiment should be conducted while inserting rest breaks as appropriate, paying attention to research subject’s level of fatigue. During the experiment, the examiner should call out to the subject as necessary, while carefully observing the subject so that the subject does not become excessively fatigued. Only occupational therapists are to perform measurements and interventions. In the unlikely event of deterioration of physical condition or excessive psychosomatic stress, the measurement will be stopped immediately. In such cases, vital measurements should be taken first, and the experiment should be stopped if the pulse rate is 120/min or higher, diastolic blood pressure is 120 mmHg or higher, or systolic blood pressure is 200 mmHg or higher, in accordance with the rehabilitation implementation criteria. Even if there is no abnormality in the vital signs, the experiment will be terminated and the subject will be excluded from the study if there is concern that their physical condition will deteriorate further due to the continuation of the experiment, based on the subject's strong sense of burden, facial expression, respiration, sweating, and so on. If the subject's sense of strain is expected to recover after a few minutes of rest, we will resume the measurement after about 5 minutes of rest, while listening to the subject's wishes. The subject should be informed that he/she has the right to refuse to continue the study, and an environment in which he/she can communicate with the subject should be maintained at all times during the measurement and intervention.

10. Method of storage and disposal of samples and information

- 1. Retention period of information, etc.

Retain the paper for 10 years after publication.

- 1. Methods of storing information, etc. (measures to prevent leakage, mixing, theft, loss, etc.)

All data analysis, etc., will be performed within the Department of Human Health Sciences, Graduate School of Medicine. A computer for research use will be purchased in the laboratory and used without Internet access to prevent leakage to the outside and loss of data. In addition, passwords will be applied to the computers to prevent theft or loss of data.

- 1. If disposed of after the storage period, the method of disposal

After the retention period ends or when consent is withdrawn, personal information and personal data are destroyed by shredding paper media or by completely deleting electronic media.

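### A judgement-based stop for strain also excludes the subject from the study after randomisation, which can remove a complete primary RSA value; nothing says that recorded data are kept

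*Protocol*

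**What the plan says.** Protocol section 9. 4) describes two kinds of stop. For the vital-sign limits it says only that the experiment is stopped. For a stop on the examiner's judgement, which applies even with normal vital signs, it gives two consequences: "the experiment will be terminated and the subject will be excluded from the study". The signs named for that judgement are "strong sense of burden, facial expression, respiration, sweating, and so on". If the strain is expected to pass, "we will resume the measurement after about 5 minutes of rest".

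Four other places bear on what this does to the analysis:

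- **Allocation** (section 5. 2), preliminary investigation): "After enrollment of study subjects who meet the eligibility criteria, the subjects will be randomly assigned to two groups". The RSA measurements and the intervention follow on day 2.
- **Blinding** (section 5. 1)): "Blinding of only the researcher in charge of statistical analysis".
- **Primary endpoint** (section 5. 4)): "Differences in the variability of RSA values due to sensory stimulation of SCP before and after the intervention", compared between arms with an unpaired t-test. No analysis set is named.
- **Order after the intervention** (section 5. 2)): "The order of the procedures is RSA measurement, EEG measurement, and POMS2, in that order". The CAB follows the next day.

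Section 8. 5) orders destruction of data when consent is withdrawn. It gives no rule for a subject whom the examiner stops.

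**The concern.** Ending a session and removing a subject from the study are separate decisions. The first protects the subject. The second decides who is compared. Section 9. 4) joins them in one sentence, so a subject can leave the comparison after allocation because of something seen during the experiment.

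Three features make this more than a loss of numbers. The judgement is subjective and is made by staff who are not blinded. The signs include respiration and sweating, which are plausibly related to an autonomic endpoint. The two arms receive deliberately different sensory exposure, so stops could be unequal. If exclusions differ by arm and relate to the RSA change, the randomised comparison is no longer protected.

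Because post-intervention RSA is recorded first, a subject stopped during EEG, POMS2 or the CAB already has a full primary value. Losing it would be avoidable.

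**Working it through.** **1. The plan's own figure.** Inputs from section 4. 3): d = 0.7, one-sided alpha 0.05, power 0.80.

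n per arm = 2(z₀.₉₅ + z₀.₈₀)² / d² = 2(1.645 + 0.842)² / 0.49 = 12.37 / 0.49 = 25.2, so 26 per arm and 52 in total. The exact noncentral t power at 26 per arm is 0.801. Allowance for loss: 52 / 0.90 = 57.8, so 58. Both stated figures reproduce. The plan adds subjects "considering the possibility of approximately 10% dropout", that is 58 − 52 = 6. With all 29 per arm analysed, power at d = 0.7 is 0.838.

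**2. What the allowance covers.** Loss unrelated to outcome costs little. Power is 0.820 at 29 against 26, and 0.796 at 29 against 23. The allowance does not cover loss related to outcome.

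**3. Illustration of outcome-related loss in one arm.** The documents give no stopping rate and no link between visible strain and the RSA change, so both are assumed. The change score Y has unit SD, with 29 per arm. A latent strain score is L = ρ(Y − arm mean) + √(1 − ρ²) × independent noise. The k subjects with the lowest L are dropped from one arm, and the one-sided t-test at 0.05 is applied. There were 40,000 trials per setting.

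Losses in the SRI arm, no true effect (shift of the mean difference in SD; rejection rate):

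| k | ρ = 0.3 | ρ = 0.5 | ρ = 1.0 (worst case) |
|---|---|---|---|
| 1 | +0.02; 0.060 | +0.04; 0.067 | +0.07; 0.091 |
| 3 | +0.06; 0.078 | +0.10; 0.103 | +0.19; 0.196 |
| 6 | +0.10; 0.102 | +0.17; 0.157 | +0.35; 0.396 |

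With k = 0 the simulated error is 0.049. The shift should scale with ρ, and it does: at k = 3, 0.5 × 0.192 = 0.096 (simulated 0.096) and 0.3 × 0.192 = 0.058 (simulated 0.059).

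The same losses in the control arm shift the result the other way. At d = 0.7, power falls from 0.84 to:

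| k | ρ = 0.3 | ρ = 0.5 | ρ = 1.0 |
|---|---|---|---|
| 1 | 0.81 | 0.80 | 0.77 |
| 3 | 0.76 | 0.72 | 0.63 |
| 6 | 0.69 | 0.60 | 0.40 |

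The row k = 6 puts the whole allowance in one arm and is extreme.

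**4. What keeping recorded data can repair.**

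| Time of stop | Complete RSA change? | Saved by keeping recorded data? |
|---|---|---|
| Before or during the pre-intervention SCP | No | No |
| During the intervention | No | No |
| During the post-intervention SCP | No, partial at most | No |
| During EEG or POMS2, or at the CAB | Yes | Yes |

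The simulation removes a complete value for every stopped subject. For a given number of stops, it is therefore an upper bound on what a change of wording can repair.

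**The case against.** The strongest reply is that the sentence stands in a participant-protection section and may mean only that participation ends. The suspension criteria in section 4 speak only of discontinuing. Early destruction of data is ordered only on withdrawal of consent. The analysis section names no exclusion, and the vital-sign stop one sentence earlier does not mention exclusion, which may point to loose wording. Which recorded values enter the t-test is often settled in an SAP, and none was available here.

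This stands in part. A reader might infer that the protocol orders recorded RSA values to be discarded; it does not say so. But exclusion is stated in addition to termination, and the document uses the word elsewhere for persons not used as subjects (section 4) and for data left out of publications (section 8. 5)). Removal from the study is the natural reading, and an SAP that kept these subjects would sit awkwardly with it.

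A reader might also infer that the trial will lose the most reactive subjects of one arm. The documents do not support that. The rule is the same for both arms. The endpoint is a pre/post change, and a subject who reacts strongly both times need not have a low change. Stops during the pre-intervention evaluation come before any arm-specific exposure. The link between visible strain and the RSA change is an assumption.

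It is also fair that numbers may be small. The subjects are healthy adults, the protocol treats such events as unlikely, and recoverable strain leads to rest and resumption. Adding subjects for expected dropout is ordinary practice and is not itself an error.

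**Conclusion.** The point holds as a defect of wording with a possible effect on the primary comparison, and it should be corrected. As written, section 9. 4) attaches exclusion from the study to a judgement-based stop after randomisation, made by unblinded staff. Following it can remove a subject whose RSA difference is already complete, and no passage says that the value is kept.

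The size is conditional on assumed one-arm loss related to the RSA change. One SRI exclusion under no true effect gives an error of about 0.06 to 0.09. Three give about 0.08, 0.10 or 0.20 at correlations 0.3, 0.5 and 1.0. The 0.20 is a worst case and should not be read as an expected error rate. The direction is open, since control-arm losses of the same kind lower power instead. Subjects stopped before the post-intervention SCP is complete have no change score whatever the wording, so only part of any bias can be repaired.

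**What to change.** Leave the stopping conditions in section 9. 4) as they are. Replace the exclusion wording with a statement that the subject takes part in no further procedures and that data recorded up to then are kept, unless consent is withdrawn under section 8. 5). In section 5. 4), add that every randomised subject with pre- and post-intervention RSA is analysed in the assigned arm, whether or not later tasks were finished. Report the number of stops by arm and time point.

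A sensitivity analysis for stopped subjects without a post-intervention value is optional and can be left to the SAP.

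The cost is a short wording change, submitted to the ethics committee as section 18 requires, and one extra line of reporting. The sample size stays at 52 evaluable and 58 enrolled, with no added procedures or staff.
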